###### **3. Method**

###### **3.1. Trial Design**

We propose to conduct an open-label trial in which 15 individuals with PTSD receive 1 week of massed CPT combined with a single dose of psilocybin (25 mg) (Figure 1). Participants will meet criteria for a diagnosis of chronic (i.e., at least six months duration) PTSD with a Clinician-Administered PTSD Scale for DSM-5 (CAPS-5) score of 50 or higher. CPT will be provided remotely twice daily (90 minutes total) over the course of a week. On the third day of the intervention, participants will come in for an in-person (6-8 hour) psilocybin dosing session. Participants will receive a total of 12 CPT sessions, 2 psychotherapy sessions related to psilocybin (preparatory and integration sessions), and one psilocybin dosing session over 7 days. The preparatory session will be completed on day 2 of the treatment week and the integration session will be completed a day after the dosing session (day 4). ​​The primary endpoint of this study will be 1 week after the end of the treatment week (week 2). All study visits including therapy sessions and psilocybin session as well as clinical assessments, will be audio and video recorded, with all recordings preserved for research, training, adherence monitoring and quality assurance purposes. We will measure clinician-assessed PTSD symptoms via Clinician-Administered PTSD Scale for DSM-5 (CAPS-5) global severity scores at baseline, the last treatment day (day 7), and at weeks 5 and 13 (follow-up). Additional outcome measures (i.e., self-reported PTSD symptoms, depression and anxiety severity, psychological function, sleep quality) and measures of putative psychological mechanisms of change (e.g., posttraumatic cognitions, experiential avoidance) will also be measured. Participants will be followed-up weekly from week 2 until week 13 (1 week until 12 weeks post-treatment). Participants will use a commercially available wearable device (Oura Ring) to collect passive data that is relevant to mental health and well-being such as physiological signals, sleep and activity patterns. For more details on the study schedule and administration of scales, please see Table 2.

[figure not shown]

**Figure 1.** Study design with timepoints.

######

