The **Dissociative Experiences Scale II (DES-II)** is a 28-item, self-report measure of dissociative experiences. Dissociation is often considered a psychological defense mechanism for victims of traumatizing events, and the scale is of particular use in measuring dissociation among people with PTSD [(75)](https://www.zotero.org/google-docs/?rwaM9V).

The **Pittsburgh Sleep Quality Index (PSQI)** is a self-rated questionnaire which assesses sleep quality and disturbances over a 1-month time interval. It consist of 19 items which are grouped into 7 components, including (1) sleep duration, (2) sleep disturbance, (3) sleep latency, (4) daytime dysfunction due to sleepiness, (5) sleep efficiency, (6) overall sleep quality, and (7) sleep medication use. Each of the sleep components yields a score ranging from 0 to 3, with 3 indicating the greatest dysfunction. The sleep component scores are summed to yield a total score ranging from 0 to 21 with the higher total score (referred to as global score) indicating worse sleep quality. In distinguishing good and poor sleepers, a global PSQI score > 5 yields a sensitivity of 89.6% and a specificity of 86.5% [(76,77)](https://www.zotero.org/google-docs/?Am3at3).

The **World Health Organization Well-Being Index, 5-item (WHO-5)** is a short and generic global rating scale measuring subjective well-being. The WHO-5 items are: (1) ‘I have felt cheerful and in good spirits', (2) ‘I have felt calm and relaxed', (3) ‘I have felt active and vigorous', (4) ‘I woke up feeling fresh and rested' and (5) ‘My daily life has been filled with things that interest me'. The respondent is asked to rate how well each of the 5 statements applies to him or her when considering the last 14 days. Each of the 5 items is scored from 5 (all of the time) to 0 (none of the time). The raw score therefore theoretically ranges from 0 (absence of well-being) to 25 (maximal well-being) [(78)](https://www.zotero.org/google-docs/?b01brn).

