The **Quality of relationships inventory (QRI)** is a self-report questionnaire used to determine the quality relationships consisting of 25 items that are evaluated on a 4-point Likert scale ranging from 1 = not true to 4 = almost always true. The 25 items yield three dimensions: Support (7 items, e.g., ‘To what extent could you turn to this person for advice about problems?’), conflict (12 items, e.g., ‘How often do you have to work hard to avoid conflict with this person?’), and depth (6 items, e.g., ‘How significant is this relationship in your life?’). The QRI takes about 5 minutes to administer [(79)](https://www.zotero.org/google-docs/?yKuTDH).

The **Inventory of psychosocial functioning (IPF)** is an 80-item self-report instrument measuring PTSD-related functional impairment in the past 30 days. There are seven functional domains evaluated: romantic relationships, family relationships, work, friendships and socializing, parenting, education, and self-care. The IPF was developed to have high content validity, to not confound PTSD symptoms and related impairment, and to not require respondent attributions regarding the cause of impairment [(80)](https://www.zotero.org/google-docs/?HTmiCY).

The **Posttraumatic Maladaptive Beliefs Scale (PMBS)** is a 15-item scale that was developed to measure maladaptive beliefs about life circumstances that may occur following trauma exposure. The scale comprises three subscales: Threat of Harm, Self-Worth and Judgment, and Reliability and Trustworthiness of Others. Scores on each subscale can be derived by summing items within each subscale. A list of subscale items and reverse-code directions are indicated on the measure. Possible scores range from 15-105, and subscale scores range from 5-35 [(81)](https://www.zotero.org/google-docs/?Ptlf2e).

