###### **7. Statistics**

###### **7.1. General Procedures and Statistical Methods**

Feasibility outcomes will be reported with descriptive statistics (i.e., counts and proportions). A minimum of 2-3 participants per month (at our single site) will be considered a sufficient recruitment rate to indicate the feasibility of a future larger multi-site trial. We will estimate the proportions of participants adherent with the protocol, that withdraw, and for data completion with a 95% CI. A full trial with this design will be deemed feasible if the lower 95% confidence limit for the rates of adherence and data completion are **≥** 80%, and if the upper limit of 95% confidence interval for the withdrawal rate is ≤ 20%. Frequencies and proportions of AEs and serious AEs will be tabulated for the total sample for each AE type. For continuous outcomes, we will report the means and standard deviations of the score and its change from baseline until the end of treatment and over the follow-up visits. We will estimate the standard deviation of PTSD severity [CAPS-5] and its within person correlation between the baseline and the end of treatment scores. The study will examine the effect size associated with psilocybin-assisted CPT in participants with PTSD, including the durability of effects on PTSD symptoms. The main analysis will be a comparison of PTSD symptoms before and after treatment. There will be analyses of changes in symptoms of depression, psychological functioning, sleep quality and PTSD severity. In week 2, the primary endpoint assessment will take place for all subjects. An independent rater not involved in therapy will administer or collect some outcome measures, and others will be based on subjects’ self-report. Baseline will be compared to the primary end point and follow up time points. This study will provide data on the impact of psilocybin in conjunction with massed CPT. Based on the outcomes, this study will primarily detect effects due to psilocybin-assisted CPT on PTSD symptoms through calculating effect sizes and significance testing. A Wilcoxon signed rank test comparing Clinician-Administered PTSD Scale for DSM-5 (CAPS-5) scores from the baseline to the primary endpoint will be the main analysis. Durability of effects will be examined by comparing changes from baseline to the assessments at 1 until 12 weeks after the final CPT session (day 7) for each PTSD subject using Friedman test, which is a non-parametric test method for repeated measures. Effects on depression symptoms, psychological functioning, trauma-related beliefs and sleep quality will also be assessed for exploratory purposes. Changes in these measures will be compared from baseline to primary endpoint for participants using Wilcoxon signed rank tests. Analyses will examine changes from baseline up to week 13 using Friedman tests. Effect sizes for the psilocybin-assisted CPT will be calculated at the primary endpoint and follow-up time points.

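### Section 7.1 tests sleep, trauma-related beliefs and functioning at week 2, but Table 2 does not collect PSQI, PMBS or IPF then; the CAPS-5 list in 3.1 also omits week 2

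*Protocol*

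**What the plan says.** **Time of the endpoint.** Section 3.1 says the "primary endpoint of this study will be 1 week after the end of the treatment week (week 2"). Section 7.1 agrees: "In week 2, the primary endpoint assessment will take place for all subjects".

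**Tests fixed at that time.** Section 7.1 makes a Wilcoxon signed rank test on CAPS-5, baseline against the primary endpoint, the main analysis. It then adds: "Effects on depression symptoms, psychological functioning, trauma-related beliefs and sleep quality will also be assessed for exploratory purposes". For those four domains it fixes the comparison: "Changes in these measures will be compared from baseline to primary endpoint for participants using Wilcoxon signed rank tests". Friedman tests over the period to week 13 follow.

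**What is collected.** Table 2 marks PSQI, PMBS and IPF at baseline, Day 7, week 5 and week 13. It marks CAPS-5, PHQ-9 and WHO-5 at week 2. Section 3.1 gives the CAPS-5 times as "at baseline, the last treatment day (day 7), and at weeks 5 and 13 (follow-up"), without week 2.

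**Recall periods.** Section 3.10.2 says that the PSQI "assesses sleep quality and disturbances over a 1-month time interval" and describes the IPF as "measuring PTSD-related functional impairment in the past 30 days". It gives no recall period for PMBS.

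**The concern.** A signed rank test works on within-person differences. If one member of the pair is never collected, there is nothing to test. Section 7.1 fixes week 2 as the second member for four domains, and the schedule leaves that cell blank for the natural measures of three of them.

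A later analysis plan cannot repair this by choosing a method. It would have to name a different time point from the one the protocol states. If that is left until data are in hand, Day 7 or week 5 could be chosen after seeing which looks better. The choice matters for PSQI and IPF, because at Day 7 their recall windows still lie mostly before treatment.

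The CAPS-5 list in 3.1 is a separate inconsistency. It omits the visit on which the main efficacy test rests, in the same paragraph that names week 2 as the primary endpoint.

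**Working it through.** The protocol states no figure for this point, so the check compares the schedule with the tests and then counts days in the recall windows.

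**1. Schedule against tests.** Table 2 has 26 visit columns: screening, eligibility confirmation, three pre-baseline weeks, baseline, eight treatment columns (Day 3 split into pre-dose and post-dose) and weeks 2 to 13. The rows below each have exactly 26 cells, so the positions are unambiguous.

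| Comparison in 7.1 | Scale | Marked in Table 2 | Week 2? |
|---|---|---|---|
| PTSD (main analysis) | CAPS-5 | Screening, baseline, Day 7, weeks 2, 5, 13 | Yes |
| Depression | PHQ-9 | Includes baseline and every week from 2 to 13 | Yes |
| Sleep quality | PSQI | Baseline, Day 7, weeks 5, 13 | No |
| Trauma-related beliefs | PMBS | Baseline, Day 7, weeks 5, 13 | No |
| Psychological functioning | IPF (if this is the measure) | Baseline, Day 7, weeks 5, 13 | No |
| Psychological functioning | WHO-5 (if this is the measure) | Includes baseline and every week from 2 to 13 | Yes |

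Of the four exploratory domains, depression can be tested as written, sleep and beliefs cannot, and functioning depends on the instrument.

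**2. CAPS-5 in 3.1 against Table 2.** After screening, 3.1 gives baseline, Day 7, week 5 and week 13. Table 2 gives baseline, Day 7, week 2, week 5 and week 13. The one difference is week 2.

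**3. Recall windows for PSQI and IPF.** Assumptions: one month is taken as 30 days; the window ends on and includes the visit day; the day before Day 1 is counted as day 0; dosing is on Day 3. A window ending on day *d* covers days *d* − 29 to *d*. The visit days for weeks 2 and 5 are assumed, since the protocol gives only the week.

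| Visit | Window (days) | Before Day 1 | Before dosing |
|---|---|---|---|
| Day 7 | −22 to 7 | 23/30 = 77% | 25/30 = 83% |
| Week 2, taken as day 14 | −15 to 14 | 16/30 = 53% | 18/30 = 60% |
| Week 5, earliest, day 29 | 0 to 29 | 1/30 = 3% | 3/30 = 10% |
| Week 5, latest, day 35 | 6 to 35 | 0/30 = 0% | 0/30 = 0% |

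A Day-7 score on either scale mostly describes the period before treatment, so its change from baseline would be pulled towards zero. Week 5 is the first scheduled visit for these scales that largely avoids this. A week-2 assessment, had one been scheduled, would have avoided it only in part.

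**The case against.** The strongest reply is that the main efficacy test is intact and the rest is minor. Much of this stands.

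- **Loss of the main comparison.** A reader might infer from 3.1 that the week-2 CAPS-5 would be missed. The documents do not support that. Section 3.1 names week 2 as the primary endpoint and sends the reader to Table 2 for the schedule; 3.13.9 makes Table 2 the follow-up schedule; 7.1 has the week-2 assessment done for every participant at a single site. What remains is an inconsistency to reconcile.
- **All baseline-to-endpoint tests fail.** A reader might generalise this way. CAPS-5 and PHQ-9 both have week-2 values, so those tests can be run.
- **Three of four domains.** This depends on IPF being the functioning measure. It is the natural reading of 3.10.2, but 7.1 does not say so, and section 2.6.2 lists IPF and WHO-5 in the same item. Only sleep and beliefs fail on any reading.
- **Other scales without a week-2 value.** DES-II, QRI, BEAQ, MPFI-24, DERS-SF and SCS-SF follow the same schedule as PSQI. The sentence fixing the tests covers only the four named domains, so their blank week-2 cells do not contradict it.
- **Day 7 as a substitute.** The protocol never proposes it. The window arithmetic is a reason to prefer week 5 when choosing a replacement; it does not show an error already made. It says nothing about PMBS.
- **SD and correlation.** Section 7.1 also plans to estimate the CAPS-5 standard deviation and "its within person correlation between the baseline and the end of treatment scores". A reader might see a mismatch with week 2, but CAPS-5 is scheduled on Day 7, so this is feasible and contradicts nothing.
- **Importance.** The primary outcome is feasibility and tolerability, the affected tests are labelled exploratory, and 15 participants are planned without a power calculation. The Friedman analyses can still use the times that are collected.

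None of this supplies a week-2 value for PSQI or PMBS.

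**Conclusion.** The point holds in limited form. The baseline-to-week-2 tests for sleep quality and trauma-related beliefs cannot be run as written, because PSQI and PMBS are not collected at week 2. The functioning test fails too if IPF is its measure, and can be run if WHO-5 is. That is two of four exploratory comparisons for certain and three on the natural reading. Separately, 3.1 and Table 2 disagree on whether CAPS-5 is assessed at week 2.

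The main CAPS-5 analysis and the depression test are unaffected under Table 2. Because the affected tests are exploratory and wording repairs them, this is a correction of moderate weight and does not threaten the trial. The preference for week 5 over Day 7 for PSQI and IPF rests on their stated recall periods and on the week-5 visit falling between days 29 and 35.

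**What to change.** 1. In 7.1, name the instrument for each of the four domains, in particular for psychological functioning.
2. In 7.1, name in advance a collected time point for each scale with no week-2 assessment. For PSQI and IPF use week 5, and report their Day-7 values descriptively. For PMBS, name either Day 7 or week 5 before data are seen; no recall period is stated that would favour one.
3. In 3.1, add week 2 to the CAPS-5 times, to agree with Table 2 and 7.1.

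This adds no visits or scales. The cost is that the PSQI and IPF comparison falls three weeks after the stated endpoint (week 5 against week 2), so it no longer lines up in time with the main CAPS-5 test. The alternative is to add PSQI, PMBS and IPF at week 2. That keeps one common time point, but it adds participant burden, and about half of the PSQI and IPF windows would still lie before Day 1 (16/30 if the visit is on day 14).

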###### **7.2. Sample Size**

Because the anticipated effect size is unknown, a formal sample size calculation cannot be completed. For this trial, it is anticipated that 15 participants will be recruited.

###### **8. Personal Digital Phenotype Analysis and Generation**

Our goal is to have a systematic investigation of DPP with an emphasis on robustness for long-term utility. We envision the DPP to be represented as a multi-dimensional vector composed of passive and active data, where each profile is unique to one another. To do so, we propose a Statistics, Information Theory, and Data-driven (SID) pipeline to develop the foundation of the DPP. The proposed SID pipeline is encapsulated in Figure 3.

## **
[figure not shown]
**

**Figure 3.** Block diagram representation of the proposed SID pipeline.

Digital Phenotype Profile (DPP) will be created through the use of SID, and will be a representation for each individual user (93). Once the Digital Phenotype Profile (DPP) is created, we enhance the analysis by proposing the personalized digital phenotype profile (pDPP) where we develop individual models for each person by incorporating their physiological data together with their self-reported affective states collected from questionnaires. Once the personal profile/model has been constructed, physiological data (such as that collected from the Oura Ring) can be used to provide insight into a person's affective state, even without any active data. The personalized digital phenotype profile (pDPP) will be used for long-term utility where we monitor the changes in physical and behavioral health of an individual participant. The application of personalized digital phenotype profile (pDPP) could allow for insights into nurses' mental well-being in a non-intrusive way that can improve mental health care and responses to stress.

###### **9. Interpretation of the Personal Digital Phenotype**

Our goal is to have a systematic investigation of personalized digital phenotype profile (pDPP) with an emphasis on robustness for long-term utility. We envision the pDPP to be represented as a multi-dimensional vector composed of passive and active data, where each profile is unique to one another. We will use analytical techniques such as robust principal component analysis (RPCA) to represent the data. In addition, robust principal component analysis (RPCA) decomposes the matrices to low- and sparse-rank representation where the low-rank representation can be considered the outliers and sparse-rank can be considered as the concise representation of the personalized digital phenotype profile (pDPP) vector. We plan to develop an algorithm to analyze the low-rank representation for anomaly detection where new additional samples are added (passive or active data) or when the personalized digital phenotype profile (pDPP) baseline varies past an accepted threshold, an alert of potential change in physical and behavioral health can be announced.

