###### **2.6.3. Exploratory**

1. To evaluate the effect of psilocybin-assisted CPT on digital physiological passive data collected through the use of a wearable device (Oura Ring).
2. To create a personal digital phenotype profile (pDPP) based on the wearable’s and clinical assessments’ data.

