###### **2.6.3.1. Personal Digital Phenotype Profile Definition**

We propose the definition of digital phenotype profile (DPP), which calculates an individual’s baseline and continuously monitors for changes in DPP characteristics derived from mathematical models. Digital phenotype profile (DPP) is a representation of a user's physical and behavioral health using the baseline data collected at the beginning of the study as reference. The models are then fine-tuned with the continuous incoming data streams. However, variations of the model representations require further investigation to ensure its accuracy and robustness. This work investigates the statistical aspect of the analysis pipeline to offer a robust DPP representation. Specifically the use of robust principal component analysis (RPCA) to extract sparse representation. The DPP is developed through our Statistical, Information Theory, and Data-driven (SID) pipeline, then is represented through the sparse-rank matrix using RPCA.

Once the DPP representation has been created, we additionally enhance this definition by proposing the term personal digital phenotype profile (pDPP) as a personalized version of the DPP, where we use collected longitudinal data to monitor the changes in physical and behavioral health of an individual participant.

The process of digital phenotyping involves building a mathematical model using the active and passive data collected from each participant. An individual model is built for each person by incorporating their physiological data together with their self-reported affective states collected from questionnaires. Once the personal profile/model has been constructed, physiological data (such as that collected from the Oura Ring) can be used to provide insight into a person's affective state, even without any active data. In the long run, such models could allow for insights into patients’mental well-being in a non-intrusive way that can improve mental health care and responses to stress.

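### Section 9 reverses the roles of the two robust PCA components, so the digital phenotype is taken from the sparse part and anomalies are sought in the low-rank part

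*Protocol*

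**What the plan says.** The second exploratory objective in Protocol section 2.6.3 is "To create a personal digital phenotype profile (pDPP) based on the wearable’s and clinical assessments’ data". RPCA is the named technique for representing that profile, and two sections say which of its components does what.

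- Section 2.6.3.1 gives the purpose: "Specifically the use of robust principal component analysis (RPCA) to extract sparse representation". The digital phenotype profile (DPP) comes out of the proposed pipeline and "then is represented through the sparse-rank matrix using RPCA".
- Section 9 assigns roles to both components of the personal profile (pDPP): "the low-rank representation can be considered the outliers and sparse-rank can be considered as the concise representation" of the pDPP vector. It acts on this assignment: "We plan to develop an algorithm to analyze the low-rank representation for anomaly detection". When new samples are added, or when the pDPP baseline moves beyond an accepted threshold, "an alert of potential change in physical and behavioral health can be announced".

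No other section gives the opposite assignment. Section 8 describes the pipeline in general terms without assigning the components.

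**The concern.** RPCA is called robust because it moves gross, isolated errors out of the structure being estimated and into a separate sparse matrix. Section 9 names the cleaned structure as the outliers and takes the matrix of removed errors as the person's profile. The term sparse-rank adds to the confusion, since the second component is sparse in its entries and not in its rank.

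Two things are at stake for exploratory objective 2. First, a profile taken from the sparse part would mainly record isolated departures. With wearable data these may well be artefacts or single unusual nights, whereas section 2.6.3.1 wants a representation of the person's health referred to their own baseline. Second, an anomaly search in the low-rank part looks where isolated anomalies have been taken out. Both work against the robustness that sections 8 and 9 set as their aim.

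**Working it through.** The protocol gives no figure on this point, so there is none to reproduce. The check compares the text with the definition of the method and then illustrates that definition.

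**Step 1: the definition.** RPCA by principal component pursuit writes the data matrix as M = L + S and minimises ||L||_* + λ||S||_1, with λ = 1/√max(m, n) for an m × n matrix. The nuclear norm ||L||_* penalises the singular values, so L is what a few shared dimensions can explain. The L1 norm ||S||_1 penalises the entries, so S holds a few large, isolated deviations.

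**Step 2: the text against the definition.**

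| Role | Definition | Section 2.6.3.1 | Section 9 |
| --- | --- | --- | --- |
| Concise structure (profile) | L, low-rank | S, sparse | S, sparse |
| Isolated outliers | S, sparse | not stated | L, low-rank |
| Component searched for isolated anomalies | S, sparse | not stated | L, low-rank |

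The profile assignment is reversed in both sections. The outlier label and the anomaly step are reversed in section 9 only.

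**Step 3: illustration with isolated spikes.** The assumed inputs are 112 days × 30 features, true rank 2, 5% of entries corrupted by ±8, no noise, and 20 simulated matrices. The 112 days match 3 pre-baseline weeks plus weeks 1 to 13, since (3 + 13) × 7 = 112. The other inputs have no source in the protocol. Here λ = 1/√112 = 0.094. Mean results (range or minimum in brackets):

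| Quantity | Standard roles | Section 9 roles |
| --- | --- | --- |
| Correlation of the profile component with the true structure | L: 0.9999 (minimum 0.9992) | S: −0.004 (−0.055 to 0.027) |
| AUC of the outlier component for corrupted against clean entries | S: 1.00 | L: 0.50 (0.45 to 0.53) |

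An AUC of 0.50 is chance.

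**Step 4: illustration with a sustained shift.** The assumed inputs are 112 days × 20 features, rank 2, 5% spikes of ±8, and a step of 2 units from day 24 in 25% to 100% of features, without noise and with noise of SD 0.5. Day 24 corresponds to dosing on treatment day 3 after 21 run-in days (21 + 3 = 24). The low-rank part took up about 82% to 100% of the step, with the lower values under noise. Its correlation with the underlying structure was 0.97 to 0.999, against roughly 0 to 0.15 for the sparse part. All isolated spikes still fell in the sparse part.

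Steps 3 and 4 together show that the low-rank part is the place to look for a lasting change of level, and the sparse part is the place to look for isolated anomalies.

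**The case against.** Several points can fairly be made for the protocol.

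1. **The change of interest may be sustained.** The alert is meant to signal a change in health, and the first exploratory objective is the effect of treatment on the wearable data. Such a change may last, and step 4 shows that a lasting shift goes mainly into the low-rank part. This stands. A reader might infer from section 9 that the alerts would miss the changes they are meant to flag, and the documents do not support that. What a search of the low-rank part misses is isolated departures, some of which may be sensor artefacts.
2. **There is a second alert route.** Section 9 also alerts when the pDPP baseline passes a threshold. That route does not search the low-rank part for outliers, so it is not void. It is affected to the extent that the pDPP itself is taken from the sparse part.
3. **The rows of the matrix are not defined.** If users were stacked, the low-rank part would be what they share and the sparse part would hold individual departures, so a profile drawn from the sparse part could be argued. The protocol wants each profile to be unique, but it does not state this layout or give this reason. Figure 3 and the cited method paper are not available here. Even so, this reading would not make the low-rank part the outliers.
4. **The simulations are built on the model they test.** Data made as low-rank plus spikes will be separated by a method designed for that model. This stands. They illustrate the definition and say nothing about how far results in this trial would be off.
5. **Section 2.6.3.1 does not repeat the whole error.** It takes the sparse matrix as the profile, but it neither labels the low-rank part nor mentions anomaly detection. This stands.
6. **The work is exploratory and the wording provisional.** Section 9 only plans to develop an algorithm, and section 2.6.3.1 says that variants of the model need further study. This lowers the weight of the point but does not correct the stated roles.

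**Conclusion.** The point holds. Section 9 assigns the two RPCA components the wrong way round, and section 2.6.3.1 shares the part that concerns the profile. This follows from the definition of the method and does not depend on any simulation setting. Followed as written, the profile would consist mainly of isolated departures and artefacts, and the anomaly search would miss isolated anomalies while still being able to show a sustained shift.

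The reach is limited to exploratory objective 2. The feasibility, CAPS-5 and safety analyses do not use the profile, and the collected data are unaffected. The conclusion about the profile assumes that RPCA is applied to one person's data over time. Under a stacked layout, use of the sparse part could be defended if stated, but the outlier label for the low-rank part could not.

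**What to change.** In sections 2.6.3.1 and 9:

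- define the low-rank component as the DPP/pDPP profile and baseline;
- use the sparse component to detect isolated anomalies;
- treat drift in the low-rank component as a change of baseline, which keeps the threshold alert in section 9;
- replace the term sparse-rank with sparse.

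If the sparse part is intended as each person's departure from a pattern shared across users, state that matrix layout, justify it, and drop the outlier label for the low-rank part.

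A particular detection rule, such as one based on the size and run length of sparse entries against the participant's own run-in period, is optional. The cost is revised wording and a swapped matrix in the code, with no change to data collection and no burden on participants.
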